#### Visits 5 and 6—Active treatment visits

Visits 5 and 6 should occur **14 ±3** days from the previous study visit. Visits 5 and 6 procedures will include:

- vital signs
- evaluation of adverse events
- safety laboratory tests
- urinalysis
- review of concomitant medications
- review of electronic diary understanding and compliance
- McGill pain questionnaire
- administer study drug in clinic (designated PK centers at Visit 6 only)
- blood collection for PK analysis (selected sites at Visit 6 only)
- rescue drug accountability
- dispense rescue medication
- study drug accountability
- dispense study drug and administration supplies (needles/syringes, alcohol wipes, sharps containers)

#### Visit 7—Crossover visit (end of active treatment phase)

Visits 7 should occur **14 ±3** days from the previous study visit. Visit 7 procedures will include:

- vital signs
- physical examination
- neurologic examination
- neuropathy assessment
- global physician impression
- nerve conduction studies
- Karnofsky performance score
- evaluation of adverse events
- review of concomitant medications
- review of electronic diary understanding and compliance
- McGill pain questionnaire
- safety laboratories
- urinalysis
- 12-lead EKG
- HIV-1 RNA
- CD4 cell count
- administer study drug in clinic (designated PK centers)
- blood collection for PK analysis (selected sites only)
- collect blood samples for prosaptide antibody levels
- rescue drug accountability
- dispense rescue medication
- study drug accountability
- dispense study drug and administration supplies (needles/syringes, alcohol wipes, sharps containers)

#### Visit 8—Final visit

Visits 8 should occur **14 ±3** days from the previous study visit. Visit 8 procedures will include:

- vital signs
- physical examination
- neurologic examination
- neuropathy assessment
- global physician impression
- McGill pain questionnaire
- evaluation of adverse events
- review of concomitant medications
- rescue drug accountability
- study drug accountability
- safety laboratories
- urinalysis
- serum ß-HCG (females of child bearing potential only)
- review electronic diary
- collection of electronic diary

#### Unscheduled visit

Any subject visit to the study site between protocol specified study visits, or for follow up of adverse events after completion of the study is termed an unscheduled visit. Subjects must complete unscheduled visit procedures specified below. Additional study procedures performed at unscheduled visits are at the discretion of the investigator.

Unscheduled visit procedures will include at least:

- review of adverse events
- review concomitant medications

#### Discontinuation visit

All subjects discontinuing from the study after administration of study drug at **Visit 4** must complete a discontinuation visit (See Section 3.4.3) for safety reasons. Discontinuation visit procedures will include:

- vital signs
- physical examination
- neurologic examination
- neuropathy assessment
- nerve conduction testing (unless Visit 7 was already completed)
- Karnofsky performance score
- McGill pain questionnaire
- global physician impression
- review of adverse events
- review concomitant medications
- 12-lead EKG
- laboratory safety tests
- urinalysis
- serum β-HCG (females of child-bearing potential only)
- HIV-1 RNA
- CD4 cell count
- review electronic diary
- prosaptide antibody
- drug accountability (rescue and study drug)
- collection of electronic diary

### 3.4.3. Subject withdrawal from study or discontinuation

It is the goal of the study that all subjects will complete blinded therapy, and will complete all follow up procedures through **Visit 8**. However, it is understood that there may be reasons that subjects may require discontinuation from the study.

#### Criteria for treatment discontinuation

Subjects can be discontinued for any of the following reasons:

1. adverse event
2. consent withdrawn
3. lost to follow up
4. non-compliance (defined by investigator judgment as significant risk of failing to comply with the provisions of the protocol that causes harm to the subject or seriously interferes with the validity of the study results)
5. protocol violation
6. administrative reason (at the discretion of the clinical investigator or sponsor)
7. treatment failure (defined as subject request to leave study due to the need for disallowed pain medication)

#### Discontinuation

Subjects may be discontinued from the study due to the criteria for treatment discontinuation listed above. A subject who discontinues from the study at any time after receiving study drug at **Visit 4** must have a **discontinuation visit** performed. A discontinuation visit should be performed as soon as possible after it has been determined that a subject will actually be discontinued from the study, even if it is before the time of the next regularly scheduled visit. The purpose of the discontinuation visit is to ensure that adequate safety information has been collected for the subject.

All discontinuations due to an adverse event with the outcome of **death** should be reported to the sponsor’s representative (PPD) immediately. Death should NOT be listed as a reason for discontinuation. Instead, the adverse event leading to death should be recorded as the reason for discontinuation.

For those subjects who die, as much information as possible should be completed on the Discontinuation visit pages of the CRF. In addition, a **serious adverse event form** should be completed for the adverse event leading to death. If an autopsy is performed, a copy of the autopsy report must be submitted to Savient (the sponsor).

Any subject **missing** more than **4 non-consecutive or** **3 consecutive doses** of study drug during a 2-week interval should be discontinued due to noncompliance.

If a subject **moves** to an area outside the region of the study center, he or she should be considered to be **lost** to follow up and discontinued from the study.

If a subject discontinues from the study and has an ongoing adverse experience at the time of discontinuation, **the subject must receive follow up for at least 2 weeks to clarify the nature of the adverse experience**. If, after a 2-week period, the adverse experience has not resolved, then a plan for further follow up of the subject will be determined by the investigator in consultation with the Protocol Chair and Savient (the sponsor).

Any subject **discontinuing** or **changing** his or her **dideoxynucleoside regimen prior to Visit 3** should be **discontinued** from study due to protocol violation. In addition, any subject **changing** his or her **long-acting opioid regimen prior to Visit 3** should be **discontinued**. After Visit 3, subjects changing their dideoxynucleoside or long-acting opioid regimen will remain on study drug and complete the study for inclusion in the intention-to-treat analysis. However, these subjects will be flagged as protocol violators and excluded from the per protocol analysis.

## 3.5. Efficacy assessments

Efficacy endpoints will include assessments of neuropathic pain as measured by the Gracely pain scale, McGill pain questionnaire and the Global Physician impression. In addition, use of rescue pain medication will be recorded. All daily assessments will be recorded by the study subject using an **electronic diary**.

### 3.5.1. Electronic diary (ED)

Subjects will be issued an electronic diary and instructed in its use at the second screening phase (see Table 3-1, Visit 2). Data captured on the ED will include the Gracely pain scale, study medication dosing, and rescue medication use. In addition, a **morning** assessment of sleep quality and an **evening** daily pain score will be captured. Data will be uploaded from each ED on a nightly basis to a central database. At each visit, use of the diary should be reviewed with the subject and any questions answered. The subject must return the ED to the study site upon completion of the study. Further details regarding the ED are available in Appendix 4.

### 3.5.2. Gracely pain scale

Subjects will be instructed to choose pain descriptors (see Table 3-3) that describe their current pain intensity from the neuropathy 13-point Gracely pain scale at the time of the random ED prompt. After Visit 2, subjects will be instructed to enter the information into the ED when prompted, approximately 5 times per day. Gracely pain scale measurements performed during **Visit 1** (prior to issuing the electronic diary) will be recorded directly on the CRF by the study subject22.

###### Table 3-3: Subject pain intensity measures (13-point Gracely pain intensity scale)

| **Letter** | **Description** | **Scale*** |
| --- | --- | --- |
| A | nothing | 0.00 |
| B | faint | 0.36 |
| C | very weak | 0.40 |
| D | weak | 0.45 |
| E | very mild | 0.59 |
| F | mild | 0.74 |
| G | moderate | 1.09 |
| H | barely strong | 1.10 |
| I | slightly intense | 1.33 |
| J | strong | 1.36 |
| K | intense | 1.54 |
| L | very intense | 1.64 |
| M | extremely intense | 1.77 |
| *log units | | |

### 3.5.3. McGill pain questionnaire

The short form of the McGill Pain Questionnaire (SF-MPQ) will be utilized in this study. It should be completed by the study subject at **Visits 2-8**. The main component of the SF-MPQ consists of 15 descriptors (11 sensory, 4 affective) which are rated on an intensity scale as 0=none, 1=mild, 2=moderate, and 3=severe. Three pain scores will be derived from the sum of the intensity rank values of the words chosen for sensory, affective and total descriptors. The SF-MPQ also includes a present pain intensity (PPI) index and a visual analog scale (VAS). An example of the SF-MPQ is found in Appendix 523.

### Global physician impression

The Global Physician impression will be completed by the neurologist evaluating the study subject at **Visits 1, 4, 7** and **8**. Physicians should rate their subject’s neuropathic pain at the time of the visit by choosing one descriptor in each category. Ideally, the same neurologist should perform all of the evaluations for a given subject in the study. Table 3-4 shows global impression scale for the severity measure. Use descriptive categories (in italics below) to identify severity.

#### Table 3-4: Global physician impression

| **Global impression** | **Severity** |
| --- | --- |
| 1 | **normal** with no peripheral neuropathy pain |
| 2 | **borderline** peripheral neuropathy pain  *e.g. intermittent paresthesias or discomfort; no functional limitation in walking; usually no pain modifying therapy* |
| 3 | **mild** peripheral neuropathy pain  *e.g. intermittent or constant neuropathic pain; mild functional limitation in exercise capacity* |
| 4 | **moderate** peripheral neuropathy pain  *e.g. constant discomfort from neuropathic pain; moderate functional limitation, e.g. cannot walk long distance; frequent nocturnal wakening* |
| 5 | **marked** peripheral neuropathy pain  *e.g. constant neuropathic pain; significant limitation of walking (short distances only); may require assistive device* |
| 6 | **severe** peripheral neuropathy pain  *e.g. neuropathic pain severe enough to require long-acting narcotic; requires assistive device - i.e., cane, walker.* |
| 7 | among the most **extreme** cases of peripheral neuropathy pain  *e.g. neuropathic pain severe enough to restrict subject to wheelchair* |

### 3.5.5. Rescue medication assessment

All subjects will receive acetaminophen 500 mg caplets as rescue medication, which may be taken up to two caplets 3 times per day (every 8 hours) up to the maximum of 100 caplets dispensed per visit (extra caplets are provided in the event that the interval between visits is extended). Subjects **should be instructed to take rescue medication only when absolutely necessary**. After Visit 2, rescue medication will be recorded in the electronic diary at the time of use. Further information with regard to rescue medication is given under Section 3.3.1, and Appendix 2.

## Safety assessments

Safety assessments will consist of monitoring and recording all adverse events and serious adverse events, the regular monitoring of safety laboratories, regular measurement of vital signs, and the performance of physical and neurological examinations. In addition, prosaptide serum antibodies and HIV-1 RNA will be measured, and nerve conduction studies, 12-lead EKGs, and the Karnofsky performance score completed. All adverse events must be recorded beginning at the time of informed consent, whether or not the subject has actually received study drug. Additional information with regard to safety assessments and recorded AEs is found under Sections 3.7.1-3.7.3.

### Laboratory evaluations

All laboratory safety tests will be performed by one central laboratory facility. Contact information for the laboratory, details about collection of samples, shipment of samples, reporting of results, and alerting of extreme values are given in the manual provided by the central laboratory facility (ICON Laboratories) supplied to each site. Appendix 6, Laboratory safety tests, lists the laboratory safety tests required during the study; the Study Flow Charts (see Table 3-1: Study flow chart, and Table 3-2: Flow chart for unscheduled and discontinuation visits) lists the visits at which these tests should be obtained.

ANY CLINICALLY SIGNIFICANT CHANGE IN LABORATORY TESTS FOUND DURING THE STUDY WILL BE EVALUATED AND A DECISION AS TO WHETHER THE SUBJECT SHOULD CONTINUE IN THE STUDY WILL BE MADE BY THE INVESTIGATOR IN CONJUNCTION WITH THE PROTOCOL CHAIR AND SAVIENT (the sponsor).

Notable abnormal values as defined in Section 7.1 (Criteria for clinically notable laboratory abnormalities) will be reported to the investigators by the central laboratory for immediate safety assessment. The purpose of these reports is to ensure investigators are made aware of any potential safety concerns regarding their patients in a timely manner. In addition, all notable abnormalities will be flagged in the study analysis according to Section 6.1.6 (Safety evaluation). Notable abnormalities which are treatment-emergent will be reported separately.

If a subject discontinues from the study for any reason after receiving study drug, laboratory tests will be performed at the **discontinuation visit**. Any new abnormal laboratory values found at the post-study evaluation must be repeated until an appropriate explanation has been made or until the values have returned to normal.

### Vital signs

Vital sign measurements will be performed at each study visit. These measurements will consist of respiratory rate, heart rate, blood pressure, temperature, and weight. Height (in bare feet or wearing only thin socks) will be measured at Visit 1.

### 3.6.3. Physical examination

A physical examination will be performed at **Visits 1, 4, 7,** and **8** (or upon discontinuation from the study). Ideally, the same clinician should perform all of the examinations for a given subject in the study. A complete physical examination will include general appearance, eyes, ears, nose, mouth/throat, neck chest/lungs, heart, abdomen, lymph nodes, extremities, vasculature and skin. More extensive examinations may be done at any time at the discretion of the investigator.

Information about the physical examination must be present in the source documentation at the study site. Significant findings that are present at Visit 1 must be included on the Medical History page of the CRF. Significant findings made after Visit 1 which meet the definition of an adverse event must be recorded on the Adverse Event page of the CRF.

### 3.6.4. Neurological examination

Neurological examinations will be performed at **Visits 1, 4, 7**, and **8** (or upon discontinuation from the study). All neurological examinations must be performed by a qualified neurologist. Ideally, the **same neurologist** should perform all of the examinations for a given subject. A complete neurological examination will include grading of sensory symptoms, grading of motor symptoms, pin sensibility, vibration sensibility using a 128-Hz tuning fork, motor function and tendon reflex testing, and cranial nerve testing. In addition, the neurologist completing the neurological examination must also complete the neuropathy assessment.

Information regarding the neurological examination must be present in the source documentation at the study site. Findings present at Visit 1 must be included on the Neurologic Examination CRF. Significant findings after Visit 1 that meet the definition of an adverse event must be recorded on the Adverse Event page of the CRF. Variations in the neurological examination and neuropathy assessment that are consistent with the underlying disease are not to be routinely captured as adverse events since they will be noted on the Neurologic Examination CRF.

### Nerve conduction studies

Nerve conduction evaluations will include unilateral antidromic sural nerve conduction and unilateral peroneal motor nerve conduction. Amplitude, latency and velocity will be calculated for both sural and peroneal nerves. These evaluations will be performed at **Visit 2** for stratification and at **Visit 7** as a safety measurement.

All nerve conduction studies must be performed by an experienced electromyographer or a technician who is under the direct supervision of an experienced electromygrapher. All studies will be assessed by the “Core Laboratory”, Washington University in St. Louis, MO.

#### Certification

Prior to performing study-related nerve conduction evaluations, each study site must be certified by the “core laboratory”. To receive certification, the site must receive “core laboratory” approval of 2 nerve conduction evaluations for HIV-uninfected control subjects. The original nerve conduction tracing will be retained by the site as source document and a copy will be faxed to the core laboratory for quality assurance. After sign off by the core laboratory, data from study subjects may be entered onto the CRF by the sites.

Details regarding procedures for nerve conduction testing are available in Appendix 7.

### Karnofsky score

The Karnofsky performance score24 will be performed at **Visit 1** as an entrance criterion and also at the end of the 6 week double blind treatment period (**Visit 7**) in order to track functional performance of study subjects. Subjects must have a Karnofsky score of ≥60 in order to enter the study. Table 3-5 displays scoring categories.

###### Table 3-5: Karnofsky performance score

| **Description** | **Score** |
| --- | --- |
| **normal** with no complaints or evidence of disease | 100 |
| able to **perform normal activity** with minor signs and symptoms of disease | 90 |
| able to **perform normal activity with effort** but with some signs and symptoms of disease | 80 |
| **cares** for self but is **unable** to perform normal activity or to do active work | 70 |
| requires **occasional assistance** but is able to care for most of own needs | 60 |
| requires **considerable assistance** and **frequent** medical care | 50 |
| requires **special care** and assistance and is disabled | 40 |
| **hospitalization** indicated although **death not imminent** but is severely disabled | 30 |
| **hospitalization necessary** and active **supportive treatment required** and is very sick | 20 |
| fatal processes progressing rapidly and is **moribund** | 10 |
| is **dead** | 0 |

## Adverse event definitions, evaluation criteria and reporting

### Adverse event definitions

#### Adverse events

An adverse event is any untoward event whether or not considered related to the use of study drug. Study drug includes the drug under evaluation, and the look-alike placebo given during active treatment of the study. **Any worsening** (i.e. **any clinically significant adverse change in frequency or intensity**) **of a pre-existing condition which is temporally associated with the use of the sponsor’s product, is also an adverse event**. Unless a worsening occurs in these baseline conditions, they should NOT be considered adverse events.

Abnormal **laboratory values** or test results constitute adverse events only if they are associated with or induce clinical signs or symptoms or require therapy, and are recorded on the Adverse Events page of the CRF under the signs, symptoms or diagnosis associated with them.

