7. Subject is actively using recreational intravenous drugs, crack cocaine, or intranasal/smoked heroin or methamphetamine.

Laboratory abnormalities

1. Subject has an absolute neutrophil count (ANC) <750/mm3 (<0.75 x 109/L).
2. Subject has hemoglobin <8.0 g/dL for males or <7.5 g/dL for females.
3. Subject has a platelet count <75,000/mm3 (<75 x 109/L). A subject with mild, chronic stable thrombocytopenia and no bleeding complications, as determined and documented by the investigator, may be enrolled with a platelet count as low as 50,000/mm3 (50 x 109/L).
4. Subject has a creatinine >1.5 x upper limit of normal (ULN).
5. Subject has AST (SGOT), ALT (SGPT), and alkaline phosphatase >5x ULN.
6. Subject has total bilirubin >1.5 x ULN. Subjects receiving indinavir, atazanavir, or other drugs with the same known effect on bilirubin levels are eligible if their total bilirubin is <5 x ULN. (Note: Savient must be contacted to discuss possible discontinuation of any subject allowed into the study with a drug-induced hyperbilirubinemia whose total bilirubin approaches 7.0 mg/dL during the study.)
7. Subject has HgbA1C >6.5.
8. Subject has serum B12 ≤200 pg/mL.

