# 7. Notable laboratory value criteria, special methods and scales

## 7.1. Criteria for clinically notable laboratory abnormalities

Safety laboratories for this study will include serum chemistry, hematology and liver function tests. Urinalysis will also be performed along with safety laboratories (see Appendix 6). Due to the advanced state of immunodeficiency and multiple concomitant medications anticipated for subjects in this study, a greater variability in laboratory tests is anticipated than would be seen in a normal adult population. In addition, it is anticipated that most subjects will have multiple other concomitant conditions that may adversely influence laboratory tests. Therefore, **determination of causality for laboratory abnormalities will be particularly difficult and will require active, ongoing clinical correlation on the part of the investigator**. The central laboratory will report the predetermined clinically notable laboratory results as specified below to the investigative site immediately. The investigator is responsible for evaluating the laboratory abnormality as a potential adverse event, and for determining required follow-up. Source records should clearly document all follow-up performed.

For the purposes of this study, **clinically notable serum chemistry** abnormalities will include blood urea nitrogen (BUN) >3 times the upper limit of normal (ULN), creatinine >3 times ULN, SGOT or SGPT >5 times ULN. Since values of total bilirubin are influenced by concomitant medications, a total bilirubin of >5 times ULN will be considered clinically notable. **Clinically notable hematology** values will include a hemoglobin of <6.9 g/dL, a total white blood cell count of <2 x 109/L or  27.75 x 109/L, and a platelet count of <50 x 109/L or 1000 x 109/L.

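### A withdrawal for an asymptomatic, untreated laboratory change has no adverse event under Section 3.7.1 and no clear safety reason code, so the link between the value and stopping is not recorded

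*Protocol*

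**What the plan says.** **Definition (Protocol Section 3.7.1, Adverse events, second paragraph).** Abnormal laboratory values or test results "constitute adverse events only if they are associated with or induce clinical signs or symptoms or require therapy". The first paragraph of the same subsection separately makes any clinically significant worsening of a pre-existing condition, temporally associated with the product, an adverse event.

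**Leaving the study on a laboratory finding.** Section 3.6.1 says "ANY CLINICALLY SIGNIFICANT CHANGE IN LABORATORY TESTS FOUND DURING THE STUDY WILL BE EVALUATED AND A DECISION AS TO WHETHER THE SUBJECT SHOULD CONTINUE" is then taken by the investigator together with the protocol chair and the sponsor. In Section 3.2.2, the note to laboratory exclusion 6 requires contact with the sponsor about "possible discontinuation of any subject allowed into the study with a drug-induced hyperbilirubinemia" when total bilirubin approaches 7.0 mg/dL.

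**Reasons for leaving (Section 3.4.3).** Seven are listed: adverse event, withdrawn consent, loss to follow-up, non-compliance, protocol violation, administrative reason and treatment failure. None names a laboratory abnormality.

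**Notable values (Section 7.1).** "The investigator is responsible for evaluating the laboratory abnormality as a potential adverse event, and for determining required follow-up". The section gives no criterion of its own for when a notable value becomes an adverse event.

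**Analysis (Section 6.1.6).** Safety rests mainly on two things: adverse-event frequency and the number of laboratory values outside predetermined ranges.

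**The concern.** The definition has two ways in, clinical signs or symptoms and need for therapy. It has no third for a value that ends treatment, although the protocol expects that some values will. For a safety comparison across doses, a laboratory change serious enough to take a subject off the study is among the more informative events. Under the stated rule it does not enter the adverse-event tables.

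The comparison matters here because Section 6.1.5 recommends the dose with the best efficacy on condition that the safety profiles of the dose groups are similar. If exits for laboratory reasons differed by dose, a reader of the adverse-event and disposition data would not see it. The laboratory tables would show the abnormal value but not that it ended participation.

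**Working it through.** No figure in the plan is in dispute, so the check sets the passages side by side.

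**1. Apply the rule to one subject.** A subject has a clinically significant laboratory change, no symptoms and no treatment for it. Under Section 3.6.1 a decision on continuation follows, with neither symptoms nor therapy required. Suppose the subject is withdrawn. Under the second paragraph of Section 3.7.1 neither condition is met, so there is no adverse event.

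**2. Reason code.** Reason 1 in Section 3.4.3 (adverse event) does not strictly apply, because there is no adverse event. The other six do not describe the case; the administrative reason is merely the most open of them.

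**3. Does other text close the gap?**
- Section 7.1 asks for evaluation as a potential adverse event, but the only test available for that evaluation is the one in Section 3.7.1.
- Section 3.7.3 expects adverse events to be found through laboratory tests, among other means. They must still be adverse events as defined.
- The amendment log shows that a sentence giving the investigator discretion to declare laboratory adverse events is not in the current text. This is context only, not an error.
- The first paragraph of Section 3.7.1 may cover a worsening pre-existing condition. The entry criteria admit subjects with chronic thrombocytopenia (platelets down to 50 x 10^9/L) and with drug-induced hyperbilirubinemia. If either worsens without symptoms or therapy, the first paragraph points to an adverse event and the second away from one.

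**4. What is and is not recorded.**

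| Item | Recorded? |
| --- | --- |
| The laboratory value | Yes: shift tables to the most extreme value and summary statistics (Section 6.1.6); tests at the discontinuation visit (Section 3.6.1) |
| Notable value | Flagged, and reported separately if treatment-emergent (Section 3.6.1), where Section 7.1 sets a threshold |
| Severity, relationship, action taken | No: Section 3.7.3 describes these for adverse events only |
| Improvement after stopping as evidence on cause | No: de-challenge in Section 3.7.2 is part of adverse-event causality assessment |
| Safety reason for leaving | Not clearly |

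Section 7.1 names no threshold for several tests in Appendix 6, such as neutrophil count, alkaline phosphatase, sodium, potassium, glucose and calcium. A withdrawal for one of these would not be flagged as notable on the stated criteria.

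**5. Size, illustration only.** The documents give no rate of laboratory-driven withdrawal. With 355 randomised and 45 assumed in the 2 mg arm, each of the four main arms has (355 - 45)/4 = 77.5 subjects. The planned 10% dropout is 7.75 per arm.

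| Assumed rate | Subjects per main arm | Share of planned dropout |
| --- | --- | --- |
| 1% | 77.5 x 0.01 = 0.8 | 10% |
| 2% | 77.5 x 0.02 = 1.6 | 20% |
| 5% | 77.5 x 0.05 = 3.9 | 50% |

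**The case against.** The best defence is that the protocol sends laboratory findings to a dedicated analysis, and does so deliberately. Section 7.1 expects unusually variable laboratory values and difficult causality in this population, so a narrow adverse-event definition is reasonable. Section 6.1.6 gives out-of-range laboratory values equal standing with adverse events, and the DSMB reports in Section 6.2 use the same parameters. All of this stands. A reader who takes Section 6.1.6 to rest mainly on adverse-event frequency alone has read half the sentence.

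A reader might also infer that Sections 3.6.1, 3.7.1 and 7.1 contradict one another. They do not. One governs continuation, one defines an adverse event and one calls for an evaluation, and all three can be followed together. The real tension lies between the two paragraphs of Section 3.7.1.

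A third tempting reading is that drug-related withdrawals are undercounted as a matter of fact, under an administrative code. The documents do not support it. No passage assigns that code; the CRF completion instructions are not shown; and an investigator may in practice record an adverse event. The earlier diabetic neuropathy trial, as summarised in Section 1.1, showed no apparent dose-related changes in hematology or clinical chemistry, which suggests that such cases may be few. How disposition is tabulated may properly be left to the SAP.

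What the defence does not supply is a stated rule that ties a laboratory value to the withdrawal it caused.

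**Conclusion.** The point holds as a gap in safety recording. On the literal text, a withdrawal for an asymptomatic, untreated laboratory change is outside the adverse-event tables, has no severity, causality or action-taken record, and has no clear safety reason. The laboratory value is not lost; its link to stopping is.

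The effect is conditional on such withdrawals occurring, and its size cannot be derived from the documents. The range of 0.8 to 3.9 subjects per main arm rests wholly on assumed rates of 1% to 5%. Sites that record an adverse event despite the definition would reduce the loss but make the count depend on the site. This is a modest defect, worth correcting because the safety comparison conditions the dose recommendation and the correction is cheap.

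**What to change.** The changes concern reporting only:

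1. **Section 3.7.1:** extend the laboratory sentence with *or lead to discontinuation of study drug or of study participation*.
2. **Section 3.4.3:** state that such withdrawals are recorded under reason 1 (adverse event). Alternatively, add a separate laboratory reason and tabulate it by arm beside adverse-event withdrawals.
3. **Section 3.7.1, first and second paragraphs:** reconcile them, so that sites know how to record asymptomatic, untreated worsening of a laboratory condition present at entry.

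A broader clause covering any abnormality that the investigator judges clinically significant is not needed for this. It would largely bring back a discretion that the current text does not contain, which is a separate and debatable choice.

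The cost is one clause, one line, one clarification and a matching CRF instruction; the adverse-event count may rise slightly. No view is taken on which laboratory change should lead to withdrawal.
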